## Abstract

**Background:**

Studies examining psychosocial and depression assessment programs in maternity settings have not adequately considered the context in which psychosocial assessment occurs or how broader components of integrated care, including clinician decision-making aids, may optimise program delivery and its cost-effectiveness. There is also limited evidence relating to the diagnostic accuracy of symptom-based screening measures used in this context. The Perinatal Integrated Psychosocial Assessment (PIPA) Project was developed to address these knowledge gaps. The primary aims of the PIPA Project are to examine the clinical- and cost-effectiveness of two alternative models of integrated psychosocial care during pregnancy: ‘care as usual’ (the SAFE START model) and an alternative model (the PIPA model). The acceptability and perceived benefit of each model of care from the perspective of both pregnant women and their healthcare providers will also be assessed. Our secondary aim is to examine the psychometric properties of a number of symptom-based screening tools for depression and anxiety when used in pregnancy.

**Methods:**

This is a comparative-effectiveness study comparing ‘care as usual’ to an alternative model sequentially over two 12-month periods. Data will be collected from women at Time 1 (initial antenatal psychosocial assessment), Time 2 (2-weeks after Time 1) and from clinicians at Time 3 for each condition. Primary aims will be evaluated using a between-groups design, and the secondary aim using a within group design.

**Discussion:**

The PIPA Project will provide evidence relating to the clinical- and cost- effectiveness of psychosocial assessment integrated with electronic clinician decision making prompts, and referral options that are tailored to the woman’s psychosocial risk, in the maternity care setting. It will also address research recommendations from the Australian (2011) and NICE (2015) Clinical Practice Guidelines.

****Trial Registration**:**

ACTRN12617000932369

## Background

One in five women experience some form of mental health morbidity during pregnancy and the first postnatal year (the perinatal period). A large meta-analysis of 28 studies reported that up to 12.7% and 21.9% of women will experience major depression during pregnancy and in the first twelve months postpartum [1], respectively, while up to 21% of women meet diagnostic criteria for at least one anxiety disorder during pregnancy [2, 3]. Recent evidence from birth cohorts in France and Australia also suggest that up to 40% of women with untreated prenatal depression continue to experience symptoms four and five years postpartum [4, 5].

The health service systems in place for routine maternity care in a number of countries have provided a unique opportunity to introduce perinatal mental health promotion, prevention and early intervention programs. In Australia, routine psychosocial assessment – a broad clinical evaluation of a woman which aims to help facilitate the provision of comprehensive, quality clinical care – is central to many of these programs. In the perinatal mental health context, such an approach encompasses enquiry into a range of risk and protective factors known to affect perinatal mental health for both mother and infant, including her current and past psychological health and social circumstances. This assessment may be enhanced by the use of relevant ‘screening’ or case detection tools, such as the Edinburgh Postnatal Depression Scale (EPDS) which asks about symptoms of depression occurring in the previous seven days [6]. The aim of this assessment is to identify the presence of current symptoms or psychosocial factors known to be associated with poorer maternal mental health so that appropriate care can be provided and outcomes for women improved [7].

In the last decade Australia has become a world leader in the development of national policy and clinical practice for perinatal mental health. Examples of key Australian national initiatives that are inclusive of routine depression screening and psychosocial assessment include the *beyondblue* National Postnatal Depression Program (2001–2005) [8], the *beyondblue* National Action Plan for Perinatal Mental Health (2008) [9] and the National Perinatal Depression Initiative (NPDI; 2008–2015), which also supported the development of Australia’s first national Clinical Practice Guidelines for Depression and Related Disorders in the Perinatal Period [7]. The need for such screening and assessment programs to be well integrated with clinical guidance for appropriate care planning, and across health care disciplines and sectors, has been highlighted [10–12].

In Sydney, where the PIPA Project is based, the SAFE START perinatal mental health policy directive and clinical practice guidelines have been in place at a number of large public maternity hospitals since 2010 [13–15], with the Integrated Perinatal Care (IPC) model of care implemented in some metropolitan settings prior to this time [16]. The SAFE START policy and guidelines specify a model of perinatal psychosocial assessment that includes psychosocial assessment at the first antenatal hospital appointment (the ‘booking-in’ visit), nominates a woman’s psychosocial ‘risk level’ and recommends further clinical action where appropriate. For women with higher levels of risk, clinical review at a multidisciplinary case discussion (MCD) meeting is required [13–15].

An evaluation of the SAFE START model of care noted a number of limitations, including an overrepresentation of ‘false positive’ women discussed at MCD meetings. In other words, women some were being referred to the MCD, when these women either did not require further assessment or referral, or could have instead been further monitored by their midwives, without discussion at MCD [17]. One potential reason for this high rate of referrals to the MCD meetings is the lower threshold set by SAFE START for further referral, which may result in inadvertent over-servicing, reduced system efficacy, increased costs through service duplication, and increased anxiety for women being incorrectly identified as ‘at risk’ [18].

In response to these limitations in the SAFE START model, an alternative approach – the Perinatal Integrated Psychosocial Assessment (PIPA) model – was developed by [name] and colleagues and will be compared with SAFE START (care as usual) in the current study.

## Methods

### Clinical context and study definitions

At the initial antenatal booking in appointment, midwives at the participating site decide whether each woman in their care requires a psychosocial referral based on their responses to the routine psychosocial assessment. Once a woman has been flagged for psychosocial referral, the mental health midwife and senior social worker allocate women to the relevant service/s at a weekly ‘triage’ meeting, according to their psychosocial presentation. Referral can be made to one or more on-site components of the maternity psychosocial service, including the multidisciplinary case discussion (MCD) meeting, psychiatry clinic, mental health midwife, social work, drug and alcohol support services and antenatal psycho educational and therapy groups (see Fig. 1).

**Fig. 1 Fig1:**
[figure not shown]
Psychosocial care pathway

For the purposes of the PIPA Project, the following definitions will apply:

*Referral:* will be defined as the initial referral made by the midwife to one or more of the on-site support options. *NOTE: Referrals to services external to the participating site are outside the scope of data collection for the current project, as are referrals made at later antenatal appointments (*i.e.*, not the initial booking-in appointment).*

*‘Correct’ referral:* a clinically appropriate referral made by the midwife, as determined by the consensus opinion of senior psychosocial clinicians at the weekly ‘triage’ and MCD meetings.

*‘Incorrect’ referral:* a clinically inappropriate referral made by the midwife, as determined by the consensus opinion of senior psychosocial clinicians at the weekly ‘triage’ and MCD meetings.

### Aims

The PIPA Project will address three primary aims and one secondary aim, as follows:

*Primary Aim 1: Clinical effectiveness outcomes:* To compare the two models of care in relation to: i) the proportion of women identified as ‘at risk’ and referred by the midwife conducting the initial psychosocial assessment to the various referral pathways (e.g., mental health midwife, social work, MCD meeting), stratified by comparable levels of risk in each model of care (see Table 1); and ii) the proportion of ‘correct’ and ‘incorrect’ referrals from the initial psychosocial assessment in each model.

**Table 1 Tab1:** Comparison of key features of the SAFE START and PIPA models of integrated psychosocial assessment

	Model of integrated psychosocial assessment	
	SAFE START model (Care as usual)	PIPA model (Alternative model)
Psychosocial assessment measures	EPDS, SAFE START psychosocial questions	EPDS, ANRQ-R (psychosocial questions); clinician concerns
Psychosocial risk levels	*Three levels of psychosocial risk, defined as:* *Level 1*: no specific vulnerabilities or risk *Level 2*: *one or more risk factors* of variable severity and significance including, but not limited to, low supports, multiple birth, financial stress, isolation, ‘mild-moderate’ depression or anxiety, history of mental health problem, young age. *Level 3*: *one or more of four complex risk factors* (domestic violence, involvement with child protection services, substance misuse, severe mental illness)	*Six levels of psychosocial risk, defined as:* *No risk*: ANRQ-R = 0; EPDS < 13 (Q10 = 0); no clinician concerns. *No risk on ANRQ-R* (ANRQ-R = 0) *but clinician concerns and/or EPDS = 13 or 14.* *Low risk*: ANRQ-R = 1–24 (excluding e,g., significant mental health history^a^) and EPDS < 15 (Q10 = 0). *Medium risk*: ANRQ-R = 1–24 (including e,g., significant mental health history^a^) and EPDS < 15 (Q10 = 0). *Medium-high risk*: ANRQ-R ≥25 (excluding any ‘complex’ risk factors^b^) or combination of ‘social’ risk factors^c^ or EPDS ≥15 (Q10 = 0) or childhood trauma and neglect. *High risk*: ANRQ-R >25 and other ‘social’ risk factors^c^ or any ‘complex’ risk factor (s)^b^ or EPDS Q10 ≥ 1.
MCD meeting referral threshold	Levels 2 and 3	High risk

*MCD* multidisciplinary case discussion meeting, *ANRQ-R* Antenatal Risk Questionnaire-Revised, *EPDS* Edinburgh Postnatal Depression Scale

^a^‘significant’ mental health history: involving professional help and/or had functional impact

^b^‘Complex’ risk factors : homelessness or housing instability; domestic violence; substance misuse; contact with child protection services

^c^‘Social’ risk factors: young maternal age (less than 20 years); no partner; booking-in appointment at >20 weeks gestation

**Table 2 Tab2:** Data collection schedule and measures

Measure	Time 1 *All women (routinely collected data)*	Time 2 *Consenting women only*	Time 3 *Health professionals only*
Demographic information^a^	X		
EPDS^a^	X	X	
Psychosocial assessment^a^	X		
Routine referral information^b,c^	X		
Feedback survey (women)^d^		X	
Costing data	X		X
Feedback survey; observational data; key informant interviews; focus groups (health professionals)^b,c,e^			X
Whooley questions^f^		X	
GAD-2^f,g^		X	
MGMQ^f,g^		X	
MINI^f,g^		X	
Interval question^f,g^		X	
Brief help seeking items^f,g^		X	

*EPDS* Edinburgh Perinatal Depression Scale, *GAD-2* Generalized Anxiety Disorder Scale-2items, *MGMQ* Matthey Generic Mood Questionnaire, *MINI* Mini International Neuropsychiatric Interview (v6.0; mood and anxiety disorder modules only; Data will be used to address: ^a^All aims; ^b^Primary Aim 1 (clinical effectiveness); ^c^Primary Aim 2 (cost effectiveness); ^d^Primary Aim 3 (pregnant women perspectives); ^e^Primary Aim 3 (health care provider perspectives); ^f^Secondary Aim (psychometric evaluation). ^g^Completed by women allocated to the PIPA model of care only

*Primary Aim 2: Cost-effectiveness outcomes:* To quantify: i) the cost per ‘correct’ and ‘incorrect’ referral made at the initial psychosocial assessment, for each model of care; ii) the incremental cost per ‘correct’ referral made and the incremental cost per ‘incorrect’ referral averted by the PIPA model compared to the SAFE START model; and, iii) the budgetary implications of implementing the PIPA model at the participating site, based on number of women assessed.

*Primary Aim 3: Consumer perspectives:* To compare the acceptability and perceived benefit of each model of care from the perspective of both pregnant women and their healthcare providers.

*Secondary Aim: Psychometric properties of screening tools:* To examine the sensitivity, specificity, positive and negative predictive values, and positive and negative likelihood ratios of the EPDS [6], ‘Whooley’ depression questions [19, 20], the Generalized Anxiety Disorder Scale [GAD-7] and its short form [GAD-2] [21], and Matthey Generic Mood Questionnaire (MGMQ) [22] when used during pregnancy, using the Mini International Neuropsychiatric Interview v6.0 [23] (MINI) as the gold standard.

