#### SAFE START model (care as usual)

This model of care recommends that all women complete the EPDS and SAFE START psychosocial questions at the initial antenatal booking-in appointment [13]. A paper-based version of the EPDS is completed by the woman and the total score and score on question 10 are manually scored by the midwife and recorded on a state-wide administrative database (ObstetriX; to be superseded by eMaternity), whereas the psychosocial questions are administered face-face by the midwife and responses electronically recorded in the database. The psychosocial questions cover seven key domains of risk: (1) (lack of) social supports; (2) recent stressors in the previous 12 months; (3) anxious personality style or low self-esteem; (4) history of mental health problems; (5) history of childhood abuse; (6) contact with child protective services or having a child living in the care of another person; and (7) current or recent domestic violence. Based on responses to these questions and the EPDS, women fall into one of three SAFE START psychosocial risk levels: Level 1 (no specific vulnerabilities or risk); Level 2 (endorsing one or more of a broad range of risk factors of variable severity and significance) or Level 3 (endorsing one or more complex risk factors, where ‘complex’ risk implies a high degree of psychosocial morbidity associated with greater risk of mental health disorder, lack of engagement with services and risk of poor parenting and infant outcomes, including risk of harm to the infant).

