### Statistical analysis

#### Clinical effectiveness, acceptability and perceived benefit analysis

Effectiveness outcomes (Primary Aim 1), including the proportion of women identified at particular psychosocial risk levels (as defined in the SAFE START and PIPA models of care) and proportion of women considered to be ‘correct’ or ‘incorrect’ referrals in each care model will be analysed using chi-square and independent-samples *t*-tests (or Mann Whitney U tests, as appropriate). This approach will also be used to examine the acceptability and perceived benefit of the SAFE START and PIPA models (Primary Aim 3). Initial checking of statistical assumptions (normality, multicollinearity, examination of outliers) will be undertaken. Chi-square analysis of subgroups of women based on risk status may also be explored. Clinically significant differences between the two models will be based upon obtaining at least medium effect sizes or absolute percentage differences of at least 15%.

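### Primary Aim 1(i) stratifies referral by risk levels whose membership rules cross between models, so stratum contrasts mix reclassification with changed referral behaviour

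*Protocol article*

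**What the plan says.** Under Aims, the first part of Primary Aim 1 is the proportion of women identified as at risk and referred by the midwife to each pathway, "stratified by comparable levels of risk in each model of care (see Table 1". Table 1 is the only basis given for calling the levels comparable.

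For SAFE START, Table 1 gives "Three levels of psychosocial risk, defined as"; for PIPA, "Six levels of psychosocial risk, defined as". SAFE START Level 3 needs one of four factors: "domestic violence, involvement with child protection services, substance misuse, severe mental illness". The PIPA complex factors, any one of which gives High risk, are in footnote b: "homelessness or housing instability; domestic violence; substance misuse; contact with child protection services". PIPA High can also be reached by EPDS question 10 scored 1 or more, or by an ANRQ-R total above 25 with social risk factors. SAFE START Level 2 is one or more risk factors "of variable severity and significance including, but not limited to, low supports, multiple birth, financial stress, isolation" and others.

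The section on key differences between the models says that PIPA uses a cumulative score and grades the severity of a number of factors for which SAFE START records only presence or absence.

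The clinical effectiveness analysis section names, among the outcomes for chi-square and similar tests, "the proportion of women identified at particular psychosocial risk levels (as defined in the SAFE START and PIPA models of care"), so each model keeps its own definitions. It sets clinical significance at a medium effect size or an absolute difference of at least 15%.

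**The concern.** Stratifying a comparison is informative when the same woman would fall in the same stratum under either arm. Here the stratum is assigned by the intervention. If PIPA moves women with intermediate referral rates into its top level, the referral proportion in that level falls even when every midwife makes the decision she would have made before. This is stage migration. A difference within a level could then be read as a change in referral practice, and judged against the 15-point criterion, when some or all of it comes from relabelling.

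The chi-square on the level proportions has a related weakness: it tests two differently defined quantities against each other. What is at stake is a named part of the first primary aim.

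**Working it through.** **The plan's own figure.** The only reproducible number nearby is the Time 1 sample: 4000 births × 0.85 completing the assessment = 3400 per model, against 3500 stated (2.9% apart). It agrees approximately, and the point does not depend on it.

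**Can the six levels be merged into the three?** Take women with a single feature and apply Table 1 and its footnotes.

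| Only feature present | SAFE START | PIPA |
|---|---|---|
| Domestic violence | Level 3 | High |
| Housing instability | Not a Level 3 factor | High |
| EPDS question 10 positive | Not a Level 3 criterion | High |
| Severe mental illness, with ANRQ-R 1–24, EPDS below 15, question 10 zero | Level 3 | Can be Medium, as a significant history |
| Significant but not severe mental health history, same scores | Level 2 | Medium |
| Multiple birth | Level 2 | Not among the ANRQ-R domains listed; may be No risk |

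If High is matched to Level 3, rows 2 and 3 are misplaced. If High is matched to anything else, row 1 is misplaced. Medium also splits across Levels 2 and 3 (rows 4 and 5), and No risk can hold Level 2 women (row 6). So no grouping of whole PIPA levels reproduces the SAFE START levels.

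**Illustration at the top level.** All shares and referral rates here are assumed; none is in the protocol. The women and their referral decisions are the same under both models, and only the label changes.

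- 6% have complex factors shared by both lists; referred 80%.
- A share *a* is Level 2 but PIPA High; referred 50%.
- A share *b* is Level 3 but not PIPA High; referred 80%.
- A share *c* is Level 2 but PIPA no-risk; referred 10%.
- 30% have other risk, middle level in both; referred 25%.
- The rest have no risk; referred 2%.

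The SAFE START top level is referred 80% by construction. The PIPA top level is (0.06 × 0.80 + *a* × 0.50) / (0.06 + *a*).

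| *a*, *b*, *c* | Overall, both models | SAFE START top | PIPA top | Difference |
|---|---|---|---|---|
| 4%, 1%, 1.5% | 16.4% | 80.0% | 0.068/0.10 = 68.0% | −12.0 points |
| 8%, 2%, 3% | 19.2% | 80.0% | 0.088/0.14 = 62.9% | −17.1 points |
| 16%, 4%, 6% | 24.9% | 80.0% | 0.128/0.22 = 58.2% | −21.8 points |

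With 3500 women per model, the top levels hold 245 and 350, 280 and 490, and 350 and 770 women. At a two-sided 5% level (assumed; the article states none), a test would reject with probability about 91%, 99.9% and nearly 100%.

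The result depends on the assumptions. If the women moved up to High were also referred 80% of the time, the top-level difference would be 0. In the central case the middle level hardly moves: 0.118/0.41 = 28.8% against 0.091/0.32 = 28.4%.

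**Illustration of the pairing.** Suppose 60% of women are low risk (referred 5%) and 30% are mid risk (referred 40%), and Level 2 holds the mid group and a third of the low group. Its referral proportion is (0.30 × 0.40 + 0.20 × 0.05)/0.50 = 26%. A PIPA band holding only the mid group shows 40%, a 14-point artefact. If PIPA Low, Medium and Medium-high are merged and hold the same women as Level 2, the band also shows 26% and the artefact is 0.

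**The case against.** The strongest reply has four parts.

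1. **A crosswalk may exist elsewhere.** Calling levels comparable implies some grouping, six levels can be merged into three, and a full protocol may hold the mapping. This partly stands. A reader might infer from three against six levels that the models share no rows; the count alone does not show that, and an unprinted mapping is no fault in an article. What remains is that the membership rules cross, so no mapping of these levels can make them equivalent.

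2. **Reclassification is part of PIPA.** A reader might infer that the stratum contrasts show reclassification and nothing about care. The protocol does not support that: its background section faults the lower SAFE START referral threshold, and scoring by accumulation and severity is a stated feature of PIPA. The defect is that the two components cannot be told apart.

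3. **The analysis section is softer than the aim.** It names the distribution of women across levels and says only that subgroup chi-squares by risk status may be explored. Stage migration in referral rates does not apply to the distribution itself. This stands as a limit on the consequences. Even so, the aim names the stratified comparison, and a cross-model test of the distribution still compares two definitions.

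4. **The numbers are assumed.** They are. A reader might take 14 or 17 points as the expected bias; the documents support no particular figure.

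A reader might also infer that Level 3 cannot be rebuilt because substance misuse is absent from the SAFE START list introduced by "The psychosocial questions cover seven key domains of risk". That is not established: Table 1 makes it a Level 3 criterion, so it may be recorded elsewhere.

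**Conclusion.** The point holds for the stratified part of Primary Aim 1(i) and for a cross-model test of the level proportions. It follows from the definitions in Table 1 and needs no assumed number. Contrasts within the models' own levels combine reclassification with any change in referral behaviour, and the planned data on those levels cannot separate them.

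The size is unknown. Assumed inputs give 0 to about 22 points, so an artefact could fall on either side of the 15-point criterion. It would be wrong to conclude that all of Primary Aim 1 is uninterpretable: the overall referral proportion among assessed women and Aim 1(ii) do not use the levels.

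**What to change.** 1. Make the unstratified referral proportion among all assessed women the main Aim 1(i) contrast. The Time 1 field for any referral, yes or no, is listed without restriction to one model.
2. For stratification, define one risk band computed identically in both periods from fields recorded in both: bands of EPDS total and question 10; the overlapping psychosocial items reduced to presence or absence (supports, recent stressors, anxious style, mental health history, childhood abuse, child protection contact, domestic violence); and age, partner status and gestation at booking.
3. Fix the rule before PIPA data collection starts. The study status section says SAFE START collection is complete and PIPA collection is still to begin.
4. Report the three SAFE START and six PIPA levels descriptively within each model, with no cross-model test.

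The cost is one derivation rule and its programming, with no new data items and no change to either model of care. The common band loses PIPA's severity grading and any item recorded in only one period, such as housing, which weakens it most at the top. Whether substance use can be included depends on checking the SAFE START extract. Matching items are not worded identically. The EPDS is on paper and hand-scored in one period, and midwife-administered and auto-scored in the other. These limits should be stated with the results.

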**Fig. 2 Fig2:**
[figure not shown]
Flow chart for the PIPA Project. ^1^ No data collection in Study Year 2 due to state-level upgrade of administrative data platform at the participating site; Training in the PIPA model will take place in the final month of Year 2; ^2^ Time 1 = approx. 12–16 weeks’ gestation; ^3^ Time 2:=2 weeks post-Time 1; ^4^ Excluded from Time 2 if: declined study Expression of Interest (EoI); EoI not asked at booking-in visit; declined participation when contacted at time of Time 2; did not meet inclusion criteria at Time 2; not contacted at Time 2 due to staffing/resource limitations; ^5^ Completed by women in Group 2 only; ^6^ To examine healthcare provider perspectives, survey, observational and key informant interview data will be collected during the final 6 months of the allocation periods for Group 1 and Group 2. Focus groups will be held approx. 3-months after the implementation of the PIPA model of care

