### Data sources, measures and procedures

#### Time 1: Initial psychosocial assessment conducted at the antenatal ‘booking in’ visit

The hospital data management system (ObstetriX and subsequently eMaternity) will be used to identify all women who attended the participating site during the data collection periods for the PIPA Project, and for whom a routine psychosocial assessment was completed. The Time 1 dataset will include: date of booking in visit and psychosocial assessment; gestation and maternal age at this time; maternal date of birth; estimated date of delivery; partner status; gravidity (including reason for pregnancy loss, where available); parity; country of birth; physical health conditions; type of conception; model of maternity care; EPDS: total and Q10 scores; EPDS: item level responses (SAFE START only); psychosocial questions: item level responses; psychosocial questions: total score (PIPA only); referral/s indicated as a result of the psychosocial assessment (yes/no); referral/s indicated as a result of the psychosocial assessment (specified; PIPA only); language; interpreter needed; financial class (public, private or overseas patient); and Time 2 Expression of Interest response (yes/no). Time 1 data will be extracted by the data manager at the participating site at approximately weekly intervals, for all women allocated to the SAFE START and PIPA models of care.

#### Time 2: Two weeks post-time 1

Women who consent to participation at Time 2 will complete the EPDS [6], the ‘Whooley’ questions [19] followed by a third ‘help’ question [20], the Generalized Anxiety Disorder Scale [GAD-7] [21], the Matthey Generic Mood Questionnaire (MGMQ) [22], an ‘interval’ question to assess perceived change in emotional wellbeing at Time 2 [27] and the Mini International Neuropsychiatric Interview v6.0 [M.I.N.I.; mood and anxiety disorder modules only] [23]. Women will also complete a short survey covering the acceptability of the psychosocial questions and assessment process.

‘Key Survey’™ will be used as the platform for data collection for all Time 2 measures *except* the M.I.N.I., which will be collected using infrastructure provided by Medical Outcomes Systems (to whom the online M.I.N.I. is copyrighted). Alternatively, these questionnaires will be administered by phone by the Research Officer verbatim, with participant responses captured in the project-specific ‘Key Survey’ and MINI instruments.

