### Study status

This study is ongoing. Data collection for the SAFE START model of care (care as usual) is complete. Data collection for the PIPA model of care (alternative model) is scheduled to commence in the first half of 2017.

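### Table 2 gives five Time 2 measures to PIPA women only, the Time 2 text gives them to everyone; if Table 2 is right, the women's acceptability comparison in Primary Aim 3 is at risk of bias from the research session

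*Protocol article*

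**What the plan says.** Primary Aim 3 is a between-model comparison: "To compare the acceptability and perceived benefit of each model of care from the perspective of both pregnant women and their healthcare providers". For women, the instrument is the feedback survey. Table 2 schedules it at Time 2 with no restriction by model, and the Time 2 procedures describe it thus: "Women will also complete a short survey covering the acceptability of the psychosocial questions and assessment process". The statistical section carries over the chi-square, t and Mann-Whitney tests of Primary Aim 1: "This approach will also be used to examine the acceptability and perceived benefit of the SAFE START and PIPA models". No adjustment is described.

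The rest of the Time 2 session is described in two ways.

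- **Restricted.** In Table 2, the GAD-2, MGMQ, MINI, interval question and brief help-seeking items carry footnote g: "Completed by women allocated to the PIPA model of care only". Note 5 to Fig. 2 points the same way: "Completed by women in Group 2 only". The figure itself is not reproduced, so the items that note 5 marks cannot be read.
- **Unrestricted.** The section on Time 2 procedures begins "Women who consent to participation at Time 2 will complete the EPDS" and continues through the Whooley questions, GAD-7, MGMQ, interval question and M.I.N.I., with no mention of model.

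Study status reports that SAFE START data collection is complete, and adds: "Data collection for the PIPA model of care (alternative model) is scheduled to commence in the first half of 2017".

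**The concern.** The extra measures serve the secondary, psychometric aim. Under Table 2 they sit within one side of a primary-aim comparison. Model of care, calendar period and session content then change together, and no analysis of the collected data can separate them.

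There are three possible routes to bias in the women's survey:

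- **Participation.** Women approached in the PIPA period may be agreeing to a session that includes a diagnostic interview, and those approached in the SAFE START period to one that does not. The protocol expects 15-20% of English-speaking women to take part and gives one rate for both periods.
- **Break-off.** If the survey comes late, women who stop early are lost from the acceptability endpoint in the PIPA period only.
- **Carry-over.** A woman who has just answered further mood and anxiety questions may let them colour her rating of the booking-visit assessment two weeks before.

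The direction cannot be predicted. Loss of less satisfied women would flatter PIPA, and irritation with the session would count against it.

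**Working it through.** **1. The protocol's own Time 2 figure.** The section on eligibility and expected sample sizes gives about 4000 births a year, 85% assessed, and 15-20% participation at Time 2. It anticipates 3500 women per model at Time 1 and 650 per model at Time 2.

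- 4000 × 0.85 = 3400 (stated 3500).
- 15-20% of 3400 = 510 to 680; 15-20% of 3500 = 525 to 700.
- 650/3500 = 18.6% and 650/3400 = 19.1%, both inside the stated range.

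The 650 is a feasibility projection and is consistent with its inputs. Nothing below disputes it.

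**2. Count of Time 2 measures in Table 2.**

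| | Measures | Number |
|---|---|---|
| Both periods (no footnote g) | EPDS, women's feedback survey, Whooley questions | 3 |
| PIPA only (footnote g) | GAD-2, MGMQ, MINI, interval question, help-seeking items | 5 |

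That is 3 measures under SAFE START and 8 under PIPA. No durations are given, so the difference in time cannot be computed.

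**3. Position of the feedback survey.** Table 2 lists it before the five extra measures, and the Time 2 text mentions it after them. Neither list is presented as an order of administration. All Time 2 measures except the M.I.N.I. are collected on one survey platform; the M.I.N.I. runs on another. Telephone administration is the alternative.

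**4. What difference would reach p<0.05?** Assumptions: 650 per model, two-sided 0.05 and common acceptability p. The protocol gives neither an alpha nor an acceptability rate.

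Threshold = 1.96 × √(2p(1−p)/650).

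- p = 0.5: 5.4 points
- p = 0.7: 5.0 points
- p = 0.8: 1.96 × √(2 × 0.8 × 0.2/650) = 1.96 × 0.0222 = 4.3 points
- p = 0.9: 3.3 points

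**5. Chance that a purely spurious shift d is significant.** With p in one model and p − d in the other, probability ≈ Φ[(d − 1.96·SE₀)/SE₁]. SE₀ uses the average proportion and SE₁ the two separate proportions. For p = 0.8 and d = 0.05, SE₀ = 0.02316 and SE₁ = 0.02312, so Φ(0.199) = 0.58.

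| Shift d | Probability, for p from 0.5 to 0.9 |
|---|---|
| 5 points | 0.44 to 0.78 |
| 7 points | 0.72 to 0.96 |
| 10 points | 0.95 to 0.999 |

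**6. A break-off illustration (all inputs assumed).** True acceptability is 80% in both models. In the PIPA period 20% stop before a survey placed last, and 55% of those who stop find the process acceptable.

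- Observed PIPA acceptability = (0.80 − 0.20 × 0.55)/0.80 = 0.8625, a spurious gain of 6.3 points.
- SE = √(0.8 × 0.2/650 + 0.8625 × 0.1375/520) = 0.0218; z = 0.0625/0.0218 = 2.9.

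**7. Against the protocol's own criterion.** The statistical section requires at least a medium effect size or at least 15 percentage points. The 6.3-point shift corresponds to Cohen's h of about 0.17 and meets neither. To create 15 points at 20% break-off, only 20% of those who stop could find the process acceptable: (0.80 − 0.20 × 0.20)/0.80 = 0.95.

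**The case against.** The strongest reply is that contamination is inferred and not documented. A reader might take the Time 2 text to mean that PIPA women rate the assessment only after finishing the MINI. The text does not say so, and the row order of Table 2 would suggest the opposite. Because the MINI runs on a separate platform, stopping there need not lose the survey. The survey also asks about the booking-visit assessment, not the research session. Administration order is a detail that an article may properly leave to the full protocol.

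A reader might also call the PIPA session much longer, on a count of 3 against 8. That overstates what is known. The GAD-2 has two items, the interval measure is one question, and the help-seeking items are described as brief. Even this content is unsettled, since the Time 2 text names the GAD-7.

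These points stand, and they limit the claim to a risk of unknown size. They do not remove it. Table 2 and the Time 2 text conflict as written. A diagnostic interview in one period only remains a real difference in what women are asked to do. The participation route does not depend on where the survey comes in the session.

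**Conclusion.** The inconsistency is certain: Table 2, with note 5 of Fig. 2 in support, restricts measures to PIPA women, and the Time 2 text does not. If the restriction is real, the women's part of the Primary Aim 3 comparison is at risk of bias from the research session. The documents give no size for that bias. Under the stated assumptions a shift of a few points could be statistically significant, but a shift below 15 points would not by itself meet the protocol's percentage criterion.

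A reader might infer that no acceptability difference could then be attributed to PIPA. The documents do not support that. The survey's position is unknown, and a spurious difference of 15 points needs extreme assumptions. The provider half of the aim uses Time 3 data and is not affected. The point is a correction of the text and an inexpensive safeguard. It shows no error in the sample size.

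**What to change.** 1. Reconcile Table 2, Fig. 2 note 5 and the Time 2 procedures text on which measures each group completes. SAFE START collection is finished, so what Group 1 received is a matter of record.
2. If the restriction is real, then before PIPA Time 2 starts, administer and submit the shared items (EPDS, Whooley questions, feedback survey) first, in the order and mode used for Group 1. Present the PIPA-only measures afterwards.
3. Do not add a second consent step between the blocks. The MINI is the reference standard for the secondary aim. Fresh agreement after symptom screening could lose it selectively and distort sensitivity and specificity.
4. Include every woman who submits the feedback survey in Primary Aim 3, whether or not she completes the rest.
5. Report Time 2 participation and completion by period. Reordering protects against break-off and carry-over, but not against differences in who agrees to take part, so readers need these figures.

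The cost is a rearranged online survey and telephone script. A small number of women may stop before the PIPA-only block, which would slightly reduce the secondary-aim sample.
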